#### **Adverse Event Reporting Period**

Adverse events that occur from the time of screening to study completion are recorded.

#### **Preexisting Condition**

A preexisting condition (one that is present at the start of the study) is recorded as an adverse event if the frequency, intensity, or the character of the condition worsens during the study period.

#### **General Physical Examination Findings**

At screening, any clinically significant abnormality is recorded as a preexisting condition. Any new clinically significant findings/abnormalities that meet the definition of an adverse event are recorded and documented as an adverse event during the trial.

CONFIDENTIAL

### **Laboratory Value Findings**

CBC, chemistry, and urinalysis values outside reference ranges at the follow-up visit or at unscheduled interim visits will be recorded as adverse events.

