## **5 Subject Selection and Withdrawal**

### **5.1 Inclusion Criteria**

#### Canine:

In order to be eligible for trial participation, the subject must:

1. Present with one or more pulmonary nodules measuring at least 1cm on radiographs consistent with metastatic disease from cytologically or histologically confirmed osteosarcoma or melanoma
2. Adequate local control of primary tumor (i.e. surgery or radiation)
3. Radiographs performed within 7 days of enrollment (Day 0)
4. Dogs > 1 year
5. Body Weight > 15 kg
6. VCOG-CTCAE v2 constitutional clinical signs < grade 2
7. Overseeing clinician deems dog able to undergo sedation for radiographs
8. CBC and Chemistry performed within 7 days of enrollment (Day 0) showing adequate organ function:
  - a. HCT > 25%, Neutrophil Count > 2,000/ul, Platelet Count > 75,000/ul,
  - b. Creatinine < ULN; bilirubin < ULN; ALT < ULN; AST < ULN
9. Urinalysis performed within 7 days of enrollment (Day 0)
10. Owner consent for dog's inclusion into the trial

CONFIDENTIAL

This material is the property of the University of California Do not disclose or use except as authorized in writing by the study sponsor

Caretaker:

In order to be eligible for participation, the pet's caregiver must be:

1.  $\geq 18$  years of age on the day of signing the informed consent
2. Able to understand the requirements of the study as determined by the investigators or research assistants
3. Able to give informed consent for on behalf of the dog for inclusion in the study
4. Able to read, understand and fill out the questionnaires
5. Able to administer trial treatment to their dog as demonstrated at the first visit

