##### Start Inhaled IL-15 Therapy:

- Physical examination
- Quality of life assessment form
- 13 mL of blood obtained for CBC, Chem and PBMC's
- CBC evaluated by trials clinician
  - No minimum cell requirements for IL-15 administration, but if clinically unwell from doxo, may delay
- Inhaled IL-15 (50ug) started in hospital followed by 2 hours monitoring (See XXX section for monitoring details)
- 14 days' supply of IL-15, required PPE, IL-15 Administration Diary sent home with owner

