## 9 Safety and Adverse Events

### 9.1 *Definitions*

#### **Adverse Event (AE)**

An *adverse event* (AE) is any symptom, sign, illness or experience that develops or worsens in severity during the course of the study. Intercurrent illnesses or injuries should be regarded as adverse events. Abnormal results of diagnostic procedures are considered to be adverse events if the abnormality:

- results in study withdrawal
- is associated with a serious adverse event
- is associated with clinical signs or symptoms
- leads to additional treatment or to further diagnostic tests
- is considered by the investigator to be of clinical significance

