### **Owner Reported Findings**

Quality of Life forms will be monitored and any reported changes in health status from baseline will be recorded as an adverse event.

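### Section 9.1 gives incompatible rules for when a laboratory value is an adverse event, which can inflate the counts behind the toxicity endpoint

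*Protocol*

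**What the plan says.** All the rules at issue stand in Protocol section 9.1, Definitions.

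- **Laboratory Value Findings:** the rule here is that "CBC, chemistry, and urinalysis values outside reference ranges at the follow-up visit or at unscheduled interim visits will be recorded as adverse events". No qualifier follows.
- **Adverse Event (AE):** "Abnormal results of diagnostic procedures are considered to be adverse events if the abnormality" meets one of five conditions. It must cause withdrawal, accompany a serious adverse event, go with clinical signs, lead to treatment or further tests, or be one that "is considered by the investigator to be of clinical significance".
- **Preexisting Condition:** a condition present at the start "is recorded as an adverse event if the frequency, intensity, or the character of the condition worsens during the study period".
- **General Physical Examination Findings:** only new findings of clinical significance that also meet the AE definition are recorded.
- **Owner Reported Findings:** "any reported changes in health status from baseline will be recorded as an adverse event".

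Section 5.1, item 8, sets the laboratory entry limits. For haematology they are fixed numbers: "HCT > 25%, Neutrophil Count > 2,000/ul, Platelet Count > 75,000/ul". For four chemistry analytes they are tied to the reference range: "Creatinine < ULN; bilirubin < ULN; ALT < ULN; AST < ULN".

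Toxicity is a secondary endpoint in section 3.3, and section 1.1 names safety among the primary endpoints. Section 3.4 assesses toxicity from owner forms, physical examination, temperature, CBC, chemistry and urinalysis. Sections 1.1 and 3.4 refer to VCOG criteria. No section says which summary of toxicity will be reported.

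**The concern.** The general definition, the preexisting-condition rule and the physical-examination rule share one logic: something must be new, worse or clinically meaningful. The laboratory rule drops all three requirements. Two staff members who follow different paragraphs of section 9.1 would record different AE counts for the same dog.

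If the laboratory rule is followed as written, the AE list mixes four things: real toxicity, abnormality already present at entry, values outside range by chance, and the lymphocyte fall that doxorubicin is given to produce. The trial has 10 dogs and no control arm, so no background rate is available to set against the total. Section 9.2 also requires every AE to be followed up, so each incidental flag carries that duty.

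The owner-report rule has a related but smaller fault. Read literally, any change from baseline counts, including improvement.

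**Working it through.** The protocol states no expected AE rate, so there is no figure to reproduce. The check has two parts.

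**1. The rules side by side**

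| Case | Laboratory rule | Other rules in 9.1 |
|---|---|---|
| Value outside range; no signs, no action taken, no link to withdrawal or a serious event, judged not clinically significant | AE | Not an AE (general definition) |
| Haematology value outside range at entry and unchanged at follow-up | AE | Not an AE if treated as a preexisting condition, since nothing worsened |
| Lymphocyte count below range after doxorubicin; no signs, no action | AE | AE only if one of the five conditions is met, for example if judged clinically significant |

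The first row is enough to establish the contradiction and needs no arithmetic. The second row can occur because the haematology entry limits are not expressed against the reference range. The protocol prints no reference ranges, so this row assumes that at least one lower reference limit lies above its cut-off.

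**2. How many values chance alone would flag**

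From the protocol (sections 7.1 and 7.2.3 to 7.2.6): CBC at Days 7, 14, 21 and 35, which is four times; chemistry at Days 7 and 21, which is twice; urinalysis at Day 21, which is once. Section 7.2.3 lists Day 7 chemistry ("13 mL of blood obtained for CBC, Chem and PBMC's"), but the Day 7 sampling instructions in section 18.2.3 name CBC only, so both counts are shown. The laboratory rule speaks of one follow-up visit in the singular; it is read here as every follow-up visit with laboratory tests.

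Assumed, not in the protocol: 10 CBC and 15 chemistry analytes per panel, and a flag probability q = 5% per value in a dog with no real change (a 95% reference range).

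Number of values per dog:
- With Day 7 chemistry: 4 × 10 + 2 × 15 = 70.
- Without it: 4 × 10 + 1 × 15 = 55.

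Expected flagged values per dog = k × q:
- 70 × 0.05 = 3.5.
- 55 × 0.05 = 2.75.

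These means do not depend on correlation between values. They exclude urinalysis, which would add to them.

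Chance of at least one flag = 1 − (1 − q)^k if values are independent. For k = 70 this is 1 − 0.95^70 = 97%; for k = 55 it is 1 − 0.95^55 = 94%. This quantity is sensitive to the assumptions. With other panel sizes, now including urinalysis (k = 4 × CBC + 2 × chemistry + 1 × urinalysis analytes):

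| CBC / chemistry / urinalysis analytes | k | q = 5% | q = 2.5% |
|---|---|---|---|
| 3 / 4 / 0 | 20 | 64% | 40% |
| 5 / 8 / 2 | 38 | 86% | 62% |
| 8 / 12 / 3 | 59 | 95% | 78% |
| 10 / 15 / 5 | 75 | 98% | 85% |
| 12 / 20 / 8 | 96 | 99% | 91% |

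With equal correlation between all values of a dog (Gaussian copula, 100,000 simulated dogs, q = 5%):

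| k | correlation 0.3 | 0.5 | 0.7 |
|---|---|---|---|
| 38 | 73% | 56% | 37% |
| 75 | 90% | 71% | 46% |

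Across these scenarios the range is about 37% to 99%. It is not a floor: correlation combined with a lower flag rate or a smaller panel would go lower. Abnormal baseline values and the effect of doxorubicin would push it up, but the protocol gives no rates for either.

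**The case against.** The strongest reply is that the laboratory paragraph governs what is recorded, not how toxicity is summarised. Sections 1.1 and 3.4 point to VCOG criteria, and a summary by grade or by seriousness need not be swamped by minor flags. Tabulation is also normally left to the analysis plan. This stands as far as it goes, and it limits what can be claimed about the endpoint. It does not remove the contradiction: grading ranks events but does not decide which paragraph makes a value an event.

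A reader might infer three stronger points, none of which the protocol supports.

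- That the toxicity endpoint is close to 100% by construction. No section defines it as the proportion of dogs with any AE, and a figure near 100% needs assumed panel sizes, an assumed flag rate and near-independence. Serial values of one analyte in one dog are unlikely to be independent.
- That an unchanged abnormal value becomes a new AE at every visit. Section 9.2 follows each event until it resolves or stabilises, which reads as one continuing event. For the same reason the mean number of AEs may be below the mean number of flagged values.
- That lymphopenia will be an AE in every dog. The protocol gives neither an expected fall nor a reference limit. Recording a drug effect is also not wrong in itself, since AEs are defined without regard to cause.

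Two smaller objections are fair. Four chemistry analytes must be below the upper limit at entry, so a flat 5% is doubtful for them. And the owner-report rule sits under a general definition limited to things that arise or get worse, so counting improvement is a literal reading and the fault is one of loose wording.

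**Conclusion.** The point holds as an internal contradiction. Section 9.1 contains one rule for laboratory AEs without qualifier and others that require clinical meaning or worsening, and nothing says which prevails. Followed as written, the laboratory rule can inflate AE counts in a 10-dog trial without a control arm, possibly to nearly every dog.

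The size is indicative. About 2.8 to 3.5 values per dog would be flagged by chance, given 95% reference ranges and 55 to 70 values per dog. The probability of at least one flag, about 37% to 99% in the scenarios tried, is too dependent on assumptions to carry the argument. The contradiction itself rests on no assumption.

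**What to change.** In section 9.1, reword the laboratory paragraph so that an out-of-range value at any follow-up or unscheduled visit is an AE only if it meets one of the five conditions of the general definition, or has worsened from the last value before doxorubicin, for example by at least one VCOG-CTCAE v2 grade. Tabulate all laboratory values against baseline, so that nothing is lost from view and the lymphocyte fall can be seen there.

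In the owner-report paragraph, replace 'changes' with 'worsening', in line with the general definition.

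The cost is a wording change in section 9.1 and matching instructions for the AE pages of the case report form. The downside is that fewer laboratory events will be listed as AEs; the tabulation against baseline makes up for this.

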### **Owner Reported Findings**

Quality of Life forms will be monitored and any reported changes in health status from baseline will be recorded as an adverse event.

### **Post-study Adverse Event**

All unresolved adverse events are followed by the investigator until the events are resolved, the subject is lost to follow-up, or the adverse event is otherwise explained. At the last scheduled visit, the investigator instructs each caregiver to report any subsequent event(s) that they, or the pet's primary veterinarian, believes might reasonably be related to participation in this study. The investigator notifies Sponsor of any death or adverse event occurring at any time after a subject has discontinued or terminated study participation that may reasonably be related to this study.

## **9.2 *Recording of Adverse Events***

At each contact with the caregiver, the investigator or research assistant seeks information on adverse events by specific questioning. Caregivers will be asked to fill out a Quality of Life form to monitor patient health.

Information on all adverse events is recorded immediately in the source document, and also in the appropriate adverse event module of the case report form (CRF and REDCap). All clearly related signs, symptoms, and abnormal diagnostic procedures results are recorded in the source document.

All adverse events occurring during the study period are recorded. The clinical course of each event is followed until resolution, stabilization, or until it is determined that the study treatment or participation is not the cause. Serious adverse events that are still ongoing at the end of the study period are followed up to determine the final outcome. Any serious adverse event that occurs after the study period and is considered to be possibly related to the study treatment or study participation is recorded and reported immediately.

## **9.3 *Reporting of Serious Adverse Events and Unanticipated Problems.***

### **9.3.1 *Investigator reporting: notifying the study sponsor***

A serious adverse event is reported to the study sponsor by telephone within 24 hours of the event. A Serious Adverse Event (SAE) form is completed by the investigator and faxed within 24 hours. The investigator keeps a copy of this SAE form on file at the study site. Report serious adverse events by phone to: [name]

At the time of the initial report, the following information is provided:

CONFIDENTIAL

This material is the property of the University of California Do not disclose or use except as authorized in writing by the study sponsor

- Study identifier
- Study Center
- Subject number
- A description of the event
- Date of onset
- Current status
- Whether study treatment was discontinued
- The reason why the event is classified as serious
- Investigator assessment of the association between the event and study treatment

Within the following 48 hours, the investigator provides further information on the serious adverse event in the form of a written narrative. This includes a copy of the completed Serious Adverse Event form, and any other diagnostic information that assists the understanding of the event.

#### **9.4 Stopping Rules**

Study participant can be discontinued from trial participation:

- If deemed clinically indicated by the attending clinician
- If requested by the owner
- Owner non-compliance with treatments or visits

#### **9.5 Medical Monitoring**

It is the responsibility of the Principal Investigator to oversee the safety of the study. This safety monitoring will include careful assessment and appropriate reporting of adverse events as noted above. Medical monitoring will include a regular assessment of the number and type of serious adverse events.

### **10 Data Handling and Record Keeping**

#### **10.1 Confidentiality**

Information about participating pets and their caregivers is kept confidential. The Health Insurance Portability and Accountability Act of 1996 (HIPAA) does not apply to the caregiver as no health care service (diagnosis or treatment) is being provided. No such protected health information (PHI) regulations currently exist for companion animals. Confidentiality of information is described in the informed consent that the caregiver signs prior to enrolling their pet in the study. In the event a caregiver withdraws informed consent, the investigator retains the ability to use all information collected prior to the revocation of consent.

#### **10.2 Source Documents**

Source data is all information, original records of clinical findings, observations, or other activities in a clinical trial necessary for the reconstruction and evaluation of the trial. Source data are contained in source documents. Examples of these original documents, and data records include: hospital records, clinical and office charts, laboratory notes, memoranda, subjects' diaries or evaluation checklists, pharmacy dispensing records, recorded data from automated instruments, copies or transcriptions certified after verification as being accurate and complete, microfiches,

CONFIDENTIAL

This material is the property of the University of California Do not disclose or use except as authorized in writing by the study sponsor

photographic negatives, microfilm or magnetic media, x-rays, subject files, and records kept at the pharmacy, at the laboratories, and at medico-technical departments involved in the clinical trial.

### ***10.3 Participant Binder***

There will be one comprehensive subject binder to contain all paperwork for the visits for each dog, as well as the study protocol. The binder will contain the following forms:

- Study Requirements Checklist
- Patient Demographic and History
- Signed and dated Owner Informed Consent
- Informed Consent Process Documentation
- Baseline Medical History
- Inclusion/Exclusion Criteria Form
- Clinical Visit Form for each visit
- Quality of Life Form for each visit
- Owner Equipment Agreement
- Initial Inhaled IL-15 Administration and Monitoring Form
- Daily Drug Administration Diary
- Protocol Deviation Form
- Subject Final Status Form

### ***10.4 Case Report Forms***

The study case report form (CRF) is the primary data collection instrument for the study. All Case Report Forms must include a subject ID on each page. All data requested on the CRF are recorded. All missing data are explained. If a space on the CRF is left blank because the procedure was not done or the question was not asked, “N/D” is written. If the item is not applicable to the individual case, “N/A” is written. All entries are printed legibly in black ink. If any entry error is made, to correct such an error, a single straight line is drawn through the incorrect entry and the correct data entered above it. All such changes are initialed and dated. Errors are not erased or whited out. For clarification of illegible or uncertain entries, the clarification is printed above the item, then initialed and dated.

### ***10.5 Electronic Data Capture***

Records will be manually entered into a REDCap database. The UCD REDCap will be used to electronically collect QOL surveys from pet owners. Adverse events, protocol deviations, Concomitant Medications, IL-15 and doxorubicin administration will also be databased in REDCap. Basic patient and owner information (ID numbers, e-mails, etc.) will be included to facilitate submission of surveys and collection of AEs.

### ***10.6 Records Retention***

It is the investigator’s responsibility to retain study essential documents for at least 5 years after initial publication of study results. All paper source documents and CRFs will be stored in individual subject-specific binders maintained on-site at the study center in a climate-controlled pass-key protected room. Each paper form will also be scanned into digital form and saved in individual subject-specific folders in encrypted form on an internet-based server that is password-

CONFIDENTIAL

This material is the property of the University of California. Do not disclose or use except as authorized in writing by the study sponsor.

protected by a two-step verification process, and a password-protected secure university network server that is backed up nightly.

## **11 Study Monitoring, Auditing, and Inspecting**

### ***11.1 Study Monitoring***

Data will be entered by the trials coordinator and monitoring provided by the study PI.

### ***11.2 Auditing and Inspecting***

The investigator will permit study-related monitoring, audits, and inspections by the IACUC/CTRB, the sponsor, government regulatory bodies, and University compliance and quality assurance groups of all study related documents (e.g. source documents, regulatory documents, data collection instruments, study data etc.). The investigator will ensure the capability for inspections of applicable study-related facilities (e.g. pharmacy, diagnostic laboratory, etc.).

Participation as an investigator in this study implies acceptance of potential inspection by government regulatory authorities and applicable University compliance and quality assurance offices.

## **12 Ethical Considerations**

This study is to be conducted according to applicable government regulations and Institutional research policies and procedures. While the US and international standards of Good Clinical Practice (FDA Title 21 part 312 and International Conference on Harmonization guidelines) apply to human research trials, much of the guidance is applicable to companion animal trials and will be conducted accordingly.

This protocol and any amendments will be submitted to a properly constituted Institutional Animal Care and Use Committee or Institutional Review Board (IRB), in agreement with local legal prescriptions, for formal approval of the study conduct. The decision of the IACUC/CTRB concerning the conduct of the study will be made in writing to the investigator and a copy of this decision will be provided to the sponsor before commencement of this study.

All caregivers for this study are provided a consent form describing this study and providing sufficient information for caregivers to make an informed decision about their own and their pet's participation in this study. See Attachments for a copy of the Owner Informed Consent Form. These consent forms will be submitted with the protocol for review and approval by the CTRB and IACUC for the study. The formal consent of a caregiver, using the CTRB and IACUC-approved consent forms, must be obtained before the animal is submitted to any study procedure. These consent forms must be signed by the caregiver and the investigator-designated research professional obtaining the consent.

## **13 Study Completion and Closeout Procedures**

Once the trial is complete, the coordinator will complete an End of Trial Review form for each subject to double check that all necessary source data is present in the file and that all required data

CONFIDENTIAL

This material is the property of the University of California Do not disclose or use except as authorized in writing by the study sponsor

has been entered into EDC. Subject source binders will be returned to the Investigator or housed in the VCCT archives, per the Investigator's discretion.

